## Abstract

**Abstract:**

**Introduction:**

Good communication is imperative to high-quality patient care, particularly for achieving positive outcomes in healthcare consultations. Evidence about communication in clinical consultations for people with motor neurone disease (MND) is limited, but the knowledge gap prevents possible improvements to communication skills that are unique to the challenges that people living with MND encounter. This research aims to better understand and improve communication experiences for patients with MND.

**Methods and analysis:**

A 24-month qualitative longitudinal study whereby data collection will explore 10–15 cases of persons living with MND. For each case, we will recruit one patient, one close person/carer and one healthcare professional for separate interviews alongside an observed clinical consultation. The patient will be interviewed three times at approximately 4–6-month intervals over 12 months to explore the changing experiences, communication challenges and impact on quality of life. Close persons and healthcare professionals will be interviewed once. Data will be analysed to draw out patterns within and between cases, incorporating thematic analysis, corpus linguistics and conversation analysis techniques.

**Ethics and dissemination:**

Ethical approval was granted by the Health Research Authority (ref: 26/WM/0026).

A co-design workshop will develop a framework for an educational toolkit for healthcare professionals to improve communication skills with MND patients. Findings will be disseminated to the academic community, healthcare staff and the public to increase reach and impact (academic journals, seminars, conferences, newsletters, community groups and engagement events). We will make recommendations for improvements to policy and practice.

**Trial registration number:**

ISRCTN15571034.

STRENGTHS AND LIMITATIONS OF THIS STUDYThe interdisciplinary multimethod analytical approach and triangulation of multiple participant groups are a strength of this study, which draws on methods from health sciences and applied linguistics.The ethical principles of this protocol and study design have been guided by the lived experience of motor neurone disease through patient and public involvement.The proposed sample size is relatively small, and there is an anticipated high dropout/loss to follow-up given the 12-month longitudinal design and the disease mortality rate.

## Introduction

### Background

 Motor neurone disease (MND) is a progressive neurodegenerative disease with an average life expectancy from diagnosis of around 2–3 years, but this can vary.^1^,^3^ The incidence of MND in the UK was estimated in a 2022 study by Burchardt *et al*^4^ as 5.69/100 000. There is currently no cure for MND,^5^ and diagnosis is determined by clinical findings alongside the exclusion of mimicking conditions.^2^ Many people living with MND (plwMND) will develop difficulties with verbal communication as the disease progresses due to muscle weakness affecting breathing and speech;^6^,^10^ this can impact how readily and easily a patient may be able to make their wishes and needs known,^7 8^ such as during advance care planning discussions.^11^ Communication has been shown to be a priority for MND patients and their carers,^8^,^1012^ and is related to quality of life.^10 13^ Subsequently, there is an evolving research base^9^ relating to the use, development and evaluation of augmentative and alternative communication for MND patients,^14^ such as eye-gaze technology.^15^ However, there seems to be a reduced focus on low-tech communication methods of support (eg, gesture, boards and pictures).^6^

Good communication between healthcare providers and patients is essential for high-quality care provision and can impact clinical outcomes.^16^,^18^ However, plwMND may experience uncertainty in terms of communication^19^ exacerbated by difficulties in physical mobility and speech. In addition to the physical needs, approximately 20%–24% of plwMND can experience cognitive changes.^20^ Where communications from healthcare professionals are poor, this may add to MND patient and carer emotional distress^21^ and compromise co-ordination^22^ and delivery of care.^8^ There is also evidence that a lack of understanding of treatment options/information communicated for people with MND can limit decision-making and involvement in advance care planning.^23^ Moreover, patients with MND may equate good communication with good healthcare provision.^8^

Studies on communicating an MND diagnosis have generally indicated that this needs to be improved.^24 25^ For MND, end-of-life outcomes are often poor in comparison to other life-limiting conditions.^25 26^ As the condition deteriorates, communication is more difficult, and the person’s cognition and behaviour are impacted^19^ so that people are often unable to participate in making their own decisions at the end-of-life.^10^ plwMND have reported fearing death due to concerns over respiratory distress, choking, communication loss, physical helplessness, dependency on others, loss of dignity and being a burden, which in turn has created suicidal intent.^24^ There are also challenges for close persons (relatives, friends…) impacting on their well-being including increased psychological distress, financial burden and limited education and training to help them as carers.^27^ Health and social care professionals can also experience numerous challenges in providing good quality end-of-life care, which may be a result of a lack of integration of care services or limited knowledge about individual needs due to communication barriers - all resulting in further reluctance of healthcare professionals to initiate discussion about end-of-life.^28^ However, despite the significance of this topic,^8 14^ research dedicated to communication between healthcare professionals and plwMND and their carers is somewhat limited, although the importance of timely, effective, empathic and sensitive communication is signposted in MND research with other foci such as well-being,^21^ decision-making,^10 22^ palliative care^29^ and advance care planning.^7^

MND research^1^ has identified a need for wider dissemination of MND information to healthcare professionals, particularly in relation to end-of-life care.^29^ A lack of knowledge among clinical staff may lead to a lack of or inappropriate adjustment of communication style and consultation to suit patients.^8 30^ A recent study by Paynter *et al*^8^ goes some way to address the gap but highlights the need to explore the impact of communication challenges for plwMND. This research will contribute towards the evidence base of the communication experiences of plwMND. Research is needed to tailor education for healthcare staff on MND-related communication strategies,^8^ which this study will address directly. Despite the direct potential patient benefit,^8 14^ the imbalance of communication-focused MND research is notable when compared with other management considerations.^2 5 24^

## Methods and analysis

### Aim, questions and objectives

Aim: to explore clinical communication experiences of plwMND and their close persons and identify recommendations for healthcare providers so that the communication needs and preferences of these patients are central to clinical care, particularly as the condition deteriorates at the end of life.

Research question: what are the clinical communication experiences of plwMND (and their close persons) with healthcare providers, and do they change through disease progression?

Objectives:

Explore the experiences of communications that plwMND and their close persons have with healthcare professionals through interviews over a period (12 months) and progression of illness trajectory, including the end of life.Observe and analyse live interactions between plwMND, their close persons and healthcare professionals to explore the patient–clinician interaction through detailed conversational analysis techniques.Synthesise findings and co-produce recommendations to inform guidance and communication training to ultimately improve communication and patient-centred care that supports care planning at the end of life.

The project launched in September 2025 with recruitment and data collection planned to commence in June 2026. The project will be completed in August 2027.

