There is no minimum time between the invitation to take part in the study, consent, and the data collection. This is because of the need for timing in such life-limiting illnesses to be participant-led so as to reduce the risk of survivorship bias and exclusion of potentially vulnerable participants.^44^ Therefore, in compliance with Health Research Authority (HRA) guidance on a proportionate approach to timeframes,^45^ particularly for this low-risk research, we accept a decision taken at the time of approach. We will make interview slots available as soon as possible after participants have expressed interest in taking part. Furthermore, participant interviews will be arranged at their preference. A maximum upper limit on this period has not been stipulated to flexibly suit participant needs and re-scheduling/cancellation where needed. However, interviews will only be conducted while sites are open for data collection, and no interviews or observations will take place after the study data period has formally closed.

The study materials clearly state that participation is voluntary and participants can decline or withdraw without reason or consequences,^23 46^ and choosing not to take part will not affect participants’ medical rights in any way. Participants can choose to withdraw participation and decline any reminders, without giving a reason, by contacting the hospital/hospice that invited them or the research team. Participants approached by the recruiting healthcare staff who do not want to take part do not need to do anything further. However, given the removal of direct identifiers and that interviews will be analysed collectively across the data set, the withdrawal period is set to end when data collection closes, although specific quotes may still be withdrawn up to publication of study outputs and/or the study ends. It will be possible to comply with this partial withdrawal request after the above withdrawal period, but it will not be possible for participants to withdraw their data in any form after publication/dissemination of study outputs or the study ends (planned 31 August 2027), whichever is first.

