### Dissemination plan

A co-design workshop at the end of the study will use the findings to inform policy guidance and develop a framework for an educational toolkit for healthcare professionals to improve communication skills with plwMND. The key outputs of the research will be: (1) The co-produced list of recommendations to help inform NICE guidance^54^ to present to policy teams to initiate change and (2) A framework to inform the design of tailored MND-related communication skills toolkit to be implemented into existing training resources for healthcare professionals and members of the public (carers, close persons, volunteers and employers). Accompanying the outputs will be academic peer-reviewed (open access) publications planned as follows: the communication challenges for plwMND and how experiences can be improved (thematic analysis); conversational analysis findings from MND clinic observations; a framework for an educational toolkit for healthcare professionals. We will communicate the findings to participants and participating sites, the study advisory group, healthcare organisations, policy-makers and the public via results summaries, social media, newsletters, University websites and conferences.

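### The 15 months from June 2026 to August 2027 can give the stated 12-month follow-up only to very early enrolees; three interviews fit at the short spacing if first interviews stop by autumn 2026

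*Protocol article*

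**What the plan says.** The section on aim, questions and objectives gives the timetable: "The project launched in September 2025", with "recruitment and data collection planned to commence in June 2026. The project will be completed in August 2027". The Consent section gives the last day, in the phrase "the study ends (planned 31 August 2027), whichever is first".

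The abstract says that patients are "interviewed three times at approximately 4–6-month intervals over 12 months". Objective 1, the strengths and limitations box, and the attrition paragraph under Ethical and safety considerations also use a 12-month period. The Study design section is looser. It says approximately 12 months and gives example interviews in month 1, months 4–6 and months 8–12.

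Two rules bear on the calendar. The Consent section says that "no interviews or observations will take place after the study data period has formally closed". The Dissemination plan says: "A co-design workshop at the end of the study will use the findings". The article prints neither a date for the data close nor a last date for a first interview.

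The plan recruits 15 patients to reach 10 completed triads, an allowance of about a third. The causes it lists are rapid progression, withdrawal or change of interest, complex symptoms, and death.

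**The concern.** The research question asks whether communication experiences change as the disease progresses, and Objective 1 extends this to the end of life. Within a patient, that information sits mainly in the later interviews. If the calendar closes before a patient's third interview is due, the interview is lost for a reason unrelated to the disease.

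Two things follow. The 12-month property, stated in several places, may describe few of the patients actually followed. And losses to the calendar would come on top of an attrition allowance that does not list them and is already fully used by the step from 15 to 10.

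**Working it through.** **Inputs from the article.** Launch September 2025; data collection from June 2026 (1 June taken as the most favourable day); end 31 August 2027; total duration 24 months; three interviews 4–6 months apart; 15 patients recruited for 10 completed triads; attrition about one third.

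**Inputs assumed, because the article does not give them.** Time kept after the last interview for final analysis and the workshop: 0, 2 or 3 months. Recruitment spread evenly over 3, 6 or 9 months.

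**The plan's own figures reproduce.** September 2025 to August 2027 is 24 months. The recruitment target is 10 / (1 − 1/3) = 15.

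**Data window.** September 2025 to the end of May 2026 uses 9 months, so 24 − 9 = 15 months remain. A start on 30 June would leave 14.

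**Follow-up span.** Three interviews have two gaps: 2 × 4 = 8 months to 2 × 6 = 12 months.

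**Enrolment window** = 15 − reserve − span. The last first interview is the data close minus the span.

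| Reserve | Data close | 12-month span | 8-month span |
|---|---|---|---|
| 0 months | 31 Aug 2027 | 3 months, to 31 Aug 2026 | 7 months, to 31 Dec 2026 |
| 2 months | 30 June 2027 | 1 month, to 30 June 2026 | 5 months, to 31 Oct 2026 |
| 3 months | 31 May 2027 | 0 months, about 1 June 2026 | 4 months, to 30 Sept 2026 |

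On the Study design section's month numbering, month 8 is 7 months after month 1. That 7-month span adds one month to each 8-month entry: 15 − 2 − 7 = 6 months and 15 − 3 − 7 = 5 months.

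**Patients with time for the full schedule, before any death or withdrawal** = 15 × min(1, window / recruitment duration). Results are for recruitment over 3 / 6 / 9 months.

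| Reserve | 12-month span | 8-month span |
|---|---|---|
| 0 months | 15 / 7.5 / 5 | 15 / 15 / 11.7 |
| 2 months | 5 / 2.5 / 1.7 | 15 / 12.5 / 8.3 |
| 3 months | 0 / 0 / 0 | 15 / 10 / 6.7 |

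For example, the 8-month span with a 3-month reserve and 6 months of recruitment gives 15 × 4/6 = 10.

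**The case against.** The strongest reply is that the plan is not rigid. Twelve is less than 15, the intervals are approximate, and the example months put the third interview as early as month 8. This stands. A reader might infer that the follow-up does not fit at all; it does, at the short spacing or with very early recruitment. What remains is that the 12-month description is then not what later enrolees would receive.

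A reader might also infer that many patients would be cut off. The article gives neither a recruitment pace nor a data close, so no such count can be derived. With recruitment over 3 months, one patient per site per month at five sites, all 15 have time for an 8-month span even with 3 months reserved.

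Nor is it shown that some patients lose the second interview. With 6 months of recruitment the last first interview falls on 30 November 2026. A second interview 4–6 months later falls by 31 May 2027, which is the close under a 3-month reserve.

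The remark in Sampling and sample size about an ongoing process concerns how many people are screened and invited for a capped sample. It does not declare recruitment open-ended.

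The consequence is also softened. Incomplete triads stay in the analysis, the carer interview, professional interview and observation occur once each, and patients are sampled at different disease stages. This keeps the patient in the study, but it does not supply the missing late interview. One might go further and argue that the target of 10 completed triads is out of reach, since one-third attrition on 10 of 15 leaves 10 × 2/3 = 6.7. That needs the assumed pace and reserve, and a definition of a completed triad as one with three patient interviews, which the article does not give.

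Finally, closing dates may stand in the full protocol, so their absence from an article is not the point here. The point is the strain between the printed dates and the printed follow-up.

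**Conclusion.** The concern holds in a limited form. The printed dates allow at most 15 months, and 12 months of follow-up leaves 3 for recruitment, final analysis and the workshop together. With nothing reserved, only patients first interviewed by the end of August 2026 can have 12 months. With 2 or 3 months reserved, the window is 1 or 0 months, and at most 5 of 15 patients could have 12 months in the scenarios tested.

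The three-interview schedule is deliverable over about 8 months, provided that first interviews end by about 31 October 2026 (2-month reserve) or 30 September 2026 (3-month reserve). Nothing printed in the article requires that. The number cut off by the calendar is not determinable: the scenarios run from 0 to 15 of 15. The dates are firm; the reserves and recruitment durations are assumptions.

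**What to change.** Before recruitment opens:

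1. State follow-up as about 8–12 months in the abstract, the limitations, Objective 1, the Study design section and the attrition paragraph. This agrees with the example months already given.
2. Set a data-collection close and a last first-interview date at least 8 months before it. With a close on 30 June 2027 this is 31 October 2026; with a close on 31 May 2027 it is 30 September 2026.
3. Keep the 4–6-month spacing for early enrolees, and use the shorter spacing only for later ones who would otherwise lose the third interview. A fixed 0, 4 and 8 months for everyone would shorten follow-up needlessly for those who could reach 12 months.
4. Report cases truncated by the calendar separately from disease-related attrition.

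No extra patients or interviews are needed. The cost is a slightly less favourable follow-up statement and a bounded recruitment window. The bound puts some pressure on maximum-variation sampling across five services, and must be squared with the Consent section, which sets no upper limit on the time to interview.

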### Study design

This is a longitudinal study comprising empirical data collection (qualitative) and co-production of a communication toolkit to aid consultations for people with MND. We completed the Consolidated criteria for Reporting Qualitative research (COREQ) checklist by Tong *et al*.^31^ Longitudinal study designs are an established approach in qualitative research^8 32^ as they can provide insights into the patients’ journey from diagnosis to death, highlighting the changing communication needs at different points in the disease trajectory. Data collection will explore 10–15 cases. Each case will aim to recruit one patient, one close person/carer and one healthcare professional for interviews and observations. The patient will be interviewed at three approximate 4–6-month intervals over ~12 months to explore the experiences, communication challenges and impact on quality of life. Close persons and healthcare professionals will be interviewed once.

Each case dataset for the longitudinal study will comprise up to six components:

Three interviews with plwMND (eg, month 1, 4–6 and 8–12).Interview with a carer or someone who supports plwMND (at any time point).Observation of clinical consultation.Interview with healthcare professional post-observation.

### Theoretical framework

A Critical Realist approach^33^ will be taken to ensure coherence of design, data analysis and impact, as well as informing the understanding of dying as a process affected by interactions between individuals and contexts.^34^ The critical realist ontology acknowledges the complexity inherent in social phenomena. Critical realism enables researchers to use in-depth information collected from qualitative interviewing methods, which we propose here to explain phenomena in the social world.^35 36^ The framework suggested by Brönnimann^37^ will inform study design to ensure the richness and complexity are captured and can be understood. Fryer’s^38^ critical realist approach to thematic analysis will be used to produce nuanced causal explanations of events and enhance reliability and reflexivity in the approach.

### Setting

There are 24 MND Care Centres and networks across England, Wales and Northern Ireland, developed by the MND Association at hospital and hospice sites that run clinics and outpatient appointments. We will recruit from hospices and hospitals within the Midlands in England UK, that provide specialist MND services, including outpatient, inpatient and day case procedures, treatments, clinics and other care and support provision.

### Sampling and sample size

We will sample five specialist MND services provided by hospitals and hospices located in the Midlands of England. To determine the participant sample size, we used the principles of the ‘information power matrix’^39^ and input from our patient and public involvement (PPI). We will purposively sample^40^ 15 adult participants at different stages in the MND trajectory and up to 15 of their carers (eg, family, friends…) and 10 healthcare professionals. We will aim for maximum variation, so that patients and carers from a range of demographic backgrounds will be invited to the study. Ideally, sampling will be evenly distributed across sites, that is, 2–3 participants of each group per site. However, this is unlikely to be practicable, particularly given size and service variation across sites in the Midlands. Therefore, there is no minimum recruitment number, but a maximum of 10 patients and 10 carers is imposed per site to avoid over-representation or the full sample being collected at a single site. The number of patients and carers to be screened and invited is not specified, as this should be ongoing until recruitment is complete. Participants will be sampled in accordance with the selection criteria in Box 1 below. Our inclusion and exclusion criteria are broad to help ensure that certain groups are not needlessly excluded and that recruitment is diverse, fair and equitable.

Box 1Study inclusion and exclusion criteriaInclusion criteria for patients:Adults (over 18 years).Able to make an informed decision to take part in the study.Able to participate in an interview (written and/or spoken).Receiving or having received specialist motor neurone disease (MND) service from a participating hospital or hospice.Inclusion criteria for carers:*Adults (over 18 years).Able to make informed consent to take part in the study.Able to participate in an interview (written and/or spoken).Identified as the primary family member or informal carer providing regular support to an individual diagnosed with MND.*****For the purposes of this study, we define a carer as the primary carer or any person (eg, informal carer, friend, relative or close person of a patient) who provides support for daily living activities (eg, cooking) or personal care (eg, washing) but is not directly employed to do so.Inclusion criteria for healthcare professionals:Working in a participating site supporting delivery of MND services.Exclusion criteria (all):Unable to consent to take part in this study.Medically too unwell to participate or otherwise deemed unsuitable for participation by the clinical team.Expressed a wish not to be contacted or involved in research.Children and young people under the age of 18 years old.

